# Effectiveness and safety of acupuncture for elderly overactive bladder population in Hong Kong: study protocol for a randomized controlled trial

**DOI:** 10.1186/s13063-018-2706-4

**Published:** 2018-07-13

**Keywords:** Acupuncture, Elderly, Nerve growth factor, Overactive bladder, Sham controlled

## Abstract

**Background:**

Overactive bladder (OAB) is defined as “urgency, with or without urge incontinence, usually with frequency and nocturia”. Acupuncture is one of the most popular alternative treatment methods for OAB. Little established evidence is available to support the effectiveness of acupuncture for OAB. This study is a pioneer randomized, double-blinded, sham-controlled trial to assess the effectiveness and safety of acupuncture in the elderly population with overactive bladder in Hong Kong.

**Methods/design:**

This is a randomized, double-center, patient and outcome assessor blinded, sham-controlled trial. The study sample size is 100 patients. Eligible subjects aged between 60 to 90 years old will be recruited into this study. All subjects will be randomly allocated into the active acupuncture group or sham acupuncture group in a 1: 1 ratio. Participants who are allocated into the active acupuncture group will receive a standardized 30-min real acupuncture treatment session for a total of 16 sessions on the top of standard routine care, whilst those who are randomized to the sham acupuncture arm will receive sham acupuncture in addition to standard routine care. Non-penetrating needles will be utilized as sham acupuncture. The primary outcome measure is the 7-day voiding diary and the secondary outcome measures are urine nerve growth factor (NGF) level, the Incontinence Impact Questionnaire (IIQ-7), Urogenital Distress Inventory (UDI-6) and OAB Symptom Score (OABSS). All outcome measures will be collected at baseline, the end of treatment and 3 months after treatment completion.

**Discussion:**

The objectives of this study include (1) to evaluate the effectiveness and safety of acupuncture treatment in patients with OAB on reduction in the frequency of incontinence episodes as derived from a 7-day voiding diary, (2) to evaluate whether acupuncture treatment could improve subjective symptoms in patients with OAB and (3) to examine the feasibility of using NGF as a biomarker for overactive bladder and test correlation with the effectiveness of acupuncture intervention. The finding of this study will provide preliminary evidence on the effectiveness and safety of acupuncture for treatment of OAB.

**Trial registration:**

Chinese Clinical Trial Registry, ChiCTR-INR-16010048. Registered on 29 Nov 2016.

**Electronic supplementary material:**

The online version of this article (10.1186/s13063-018-2706-4) contains supplementary material, which is available to authorized users.

## Background

Overactive bladder, also known as OAB, or overactive bladder syndrome, is defined as “urgency, with or without urge incontinence, usually with frequency and nocturia” by the International Continence Society (ICS) [1]. OAB is usually classified into two different types, i.e. OAB dry and OAB wet type according to the clinical symptoms. OAB dry is defined as having ≧ 4 episodes of urgency in the previous 4 weeks with either frequency > 8 times per day or the use of ≧ 1 coping behavior to control bladder function. OAB wet meets all the criteria of the OAB dry, but with the addition of ≧ 3 episodes of incontinence in the past 4 weeks that are clearly not caused by stress incontinence [1].

A study by Emmons and Otto reported that around 17% of Americans suffered from OAB [2]. Stewart et al. demonstrated that the prevalence of OAB with and without urge incontinence in patients in the USA is age-specific, especially in the female population [3]. OAB with urge incontinence in women at 65–74 years of age was nine times as much as that in women at age 18–24 years [3]. On the other hand, a steady increase in the prevalence of OAB with advancing age has also been observed in the male population. According to “World Population Aging 2015”, in Hong Kong the population aged 60 years or more reached 21.7% of the total population by 2015 [4]. With the pace of population aging gathering speed, it is expected that there will be more patients with OAB in Hong Kong in the coming decades. In a recent study in Hong Kong, around 15% of the population was found to suffer from OAB [5]. The economic burden resulting from managing OAB in Hong Kong will be huge in the foreseeable future. Moreover, OAB can also cause severe social impact and lead to impaired quality of life for those sufferers [6].

The current treatment methods for OAB include pharmacological therapy, behavioral therapy and physical therapy. Unfortunately, the outcome of these methods is unsatisfactory. Medication is one of the most commonly used treatment methods in Hong Kong. Presently, anticholinergics remain the mainstay therapeutic drugs for OAB; however, these are only partially effective [2]. Moreover, these drugs have considerable side effects such as dry mouth, dry eye, cessation of perspiration or even cause photophobia or confusion. On the other hand, although a number of studies have reported that behavioral therapy and physical therapy are effective, their treatment effects are usually not sustainable, and usually decline 3 months after treatment [2].

Worldwide, acupuncture is perhaps the most popular alternative treatment method in OAB. Indeed, neurogenic bladder dysfunction is one of the indications for acupuncture recommended by the World Health Organization (WHO) [7]. Today, acupuncture is one of most widely practiced alternative and complementary treatment modalities in the Asia-Pacific region. Moreover, some clinical trials have been conducted to evaluate the effectiveness and the safety of acupuncture for the treatment of OAB. A pilot study conducted by Engberg et al. suggested that acupuncture may have a clinical meaningful effect on urge incontinence [8]. A clinical case report (*n* = 11) by Kitakoji et al. illustrated that acupuncture may elicit an improvement in OAB symptoms [9]. Furthermore, a comprehensive systematic review by the Agency for Healthcare Research and Quality of the U.S. Department of Health and Human Services on the treatment of OAB in women concluded that acupuncture produced intriguing results in relation to a decreased frequency of voiding and reduced symptoms of urgency, which were associated with changes in cystometrics [10]. These previous clinical trials and systematic review indicate that acupuncture has a potentially clinically meaningful treatment effect on OAB.

Nevertheless, several limitations of these studies may potentially bias the results and render the findings inconclusive. First, many studies were open-label trials or single blinded, i.e. with blinding not applied to patients or outcome assessors [2, 11, 12]. Second, some of the studies did not use a control arm. Third, the sample size of many trials was generally small [2, 12]. Fourth, many studies used the technique of sham acupuncture involving the penetration of skin on the non-specific acupuncture points, which the authors believed would not produce treatment effect [2]. However, it is well-known that any acupuncture involving penetration of the skin, regardless of whether or not the acupuncture points are specific, can elicit a physiologic response, hence a treatment effect [13]. Fifth, most of these studies focused only on female sufferers, and few evaluated the efficacy of acupuncture in male OAB sufferers [2, 8, 12, 14]. Last, the lack of objective outcome assessment for the outcome measurement is a major drawback of the previous studies of acupuncture for treatment of OAB.

Until now, there has been no appropriately designed clinical study to investigate the effectiveness and safety of traditional acupuncture treatment for OAB. There is a clear need to fill this knowledge gap. Based on the aforementioned points, a full-scale double-blind randomized controlled trial is urgently needed to establish evidence on the effectiveness and safety of acupuncture for treating OAB.

### Objectives

The primary objective of this proposed study is to evaluate the effectiveness of acupuncture treatment in patients with OAB on reduction in the frequency of incontinence episodes as recorded in a 7-day voiding diary.

The secondary objectives are to evaluate the safety of acupuncture treatment, determine whether acupuncture treatment could improve the subjective symptoms in patients with OAB, as well as to examine the feasibility of using nerve growth factor (NGF) as a biomarker for overactive bladder and to test correlation between this and the effectiveness of the intervention.

### Strengths and limitations of this study

The strengths of the study are as follows:This is a pioneer study to evaluate the effectiveness of acupuncture for treatment of overactive bladder using an objective outcome measure viz. urinary NGF, and to test correlation between urinary NGF and subjective symptoms.Most of the previous studies focused on female sufferers, whereas the proposed study includes both male and female patients. More solid evidence could be established on the effectiveness of acupuncture in treating OAB.A non-penetrative sham acupuncture device will be utilized in this study to get rid of an unexpected physiologic responseRandomization is used to balance patients across two treatment groups.

The limitation of the study is that owing to the nature of acupuncture, it is not feasible to blind the acupuncturists who conduct the treatment procedure.

## Methods/design

### Study design

This is a double-center, patient and outcome assessor blinded, randomized, sham controlled trial to evaluate the effectiveness and safety of acupuncture treatment in patients with OAB, in Hong Kong. All eligible subjects (*n* = 100) will be randomly allocated to the intervention group (*n* = 50) or control group (*n* = 50) in a 1: 1 ratio. All subjects, both in the intervention and control group, would receive standard routine care. In the Hong Kong hospital setting, behavioral therapy and physical therapy are usually the standard routine care for overactive bladder. Acupuncture treatment will be either conducted in the Yan Oi Tong - The Chinese University of Hong Kong Chinese Medicine Centre for Training and Research in Tuen Mun (YOT-CUHKCMCTR) or The Chinese University of Hong Kong Chinese Medicine Specialty Clinic cum Clinical Teaching and Research Centre (CUHK-CMSCCTRC). This project is approved by the New Territories West Cluster Clinical and Research Ethics Committee of Hong Kong (NTWC/CREC/15147) and CUHK-New Territories East Cluster Clinical and Research Ethics Committee of Hong Kong (NTEC/CREC/2017.199-T). Written informed consent is obtained from each participant. The study will be undertaken in compliance with the principles of the International Conference on Harmonization (ICH) Good Clinical Practice (GCP) guidelines and the Declaration of Helsinki and is expected to be accomplished within a period of 24 months (Additional file 1).

### Participants

Patients who are diagnosed as having OAB and fulfill all the inclusion criteria and meet none of exclusion criteria (listed below) will be eligible to participate in the study. The diagnosis of the patients will be confirmed by two co-authors ([name] and [name]) who are specialists in geriatrics.

### Subject recruitment

Patients will be recruited from the Geriatric Day Hospital and the Urology Specialist Clinic at Tuen Mun Hospital, CUHK-CMSCCTRC, YOT-CUHKCMCTR and other affiliated Chinese medicine clinics under the management of Yan Oi Tong.

As a back-up plan, we will also aim to recruit suitable patients from the community and the elderly centers in Hong Kong through advertisements. Moreover, our research team will approach Hong Kong OAB Associations to facilitate the recruitment process. Furthermore, we will also hold promotional talks in the community and write articles in the health column of local newspapers to boost subject recruitment if the number of subjects is not sufficient.

For the logistics of subject recruitment, a research assistant will go to the Geriatric Day Hospital and the Urology Specialist Clinic at Tuen Mun Hospital twice a week to identify and invite potentially eligible patients to participate in the study. The patients will be informed of the details of the study such as the objectives, scope, procedure and potential benefits and risks. The patient will be given a written informed consent form. Patients or their caretakers will be informed of all the details and potential risks of the study, and the written informed consent form will be signed and witnessed by the research assistant. Oral informed consent may be acceptable if the participants cannot read.

### Inclusion criteria

Patients will be eligible for inclusion if they are:Male or female and are between 60 and 90 years old;Suffering from OAB wet type with urge-associated incontinence at least twice during a 3-day period;Physically and mentally able to complete the 7-day voiding diary, Urinary Distress Inventory (UDI-6), Overactive Bladder Symptom Score (OABSS) and Incontinence Impact questionnaire (IIQ7); andAble to give written informed consent.

### Exclusion criteria

Patients will be excluded based on the following:OAB symptoms caused by stroke or spinal injury;Life threatening infection;Unconsciousness or severe cognitive deficits;Dementia caused by Alzheimer’s disease or other neurodegenerative diseases;Previous incontinence surgery;On short-term active diuretic treatment or taking diuretic medication;Previous acupuncture treatment for OAB;Current drug treatment for OAB;Diagnosis of stress urinary incontinence;Suffering from untreated urinary tract infection, urogenital tumors, prostate tumor, benign prostatic hyperplasia or chronic urinary retention; andImmobility problems.

### Withdrawal criteria

The withdrawal criteria will be:Participant’s decision to drop out from study at any time for any reason;Non-adherence of participants to the treatment protocol - patients who complete < 80% of the treatment session; andOccurrence of any unexpected serious side effects.

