### Randomization and allocation concealment

The included participants will be randomly allocated to either the active acupuncture group (intervention group) or sham acupuncture group (placebo-control group) after the baseline assessment. We will use a computer program (Random Allocation Software, version 1.0; Msaghaei) [15] to generate random numbers. Block randomization will be used to ensure a balance in the number between the two groups. The list of randomization numbers will be kept by research staff who will be responsible for assigning the recruited patients to the corresponding intervention code based on the list. He or she will not be involved in patient care, outcome assessment, data collection or data analysis. The study flowchart is shown in Fig. 1.

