#### Active acupuncture group

Sterile disposable stainless steel needles of various lengths and diameters (Huatuo, Suzhou, China; 0.3 mm × 25 mm/0.3 mm × 40 mm/0.3 mm × 75 mm) will be used in the intervention group. The acupuncture treatment will be administered twice per week, which mimics the clinical practice of using acupuncture treatment for OAB in many Chinese medicine clinics in Hong Kong, and the whole treatment period will last for 8 consecutive weeks. A total of 16 sessions of acupuncture treatment will be administered to each participant.

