### Statistical analysis

All analyses will be conducted according to the intention-to-treat principle. Descriptive statistics will be computed for each of the analyzed variables. The baseline characteristics will be tabulated and some of large differences between the two groups will be noted and examined in the general mixed model. The generalized linear mixed model will be used to compare primary and secondary outcomes between groups and test correlation between baseline factors, including NGF level, and the primary and secondary outcomes. Per-protocol analysis will be also performed. All statistical tests will be two-sided, and *p* < 0.05 is considered statistically significant. The statistical software of SPSS (SPSS, SPSS Inc., Chicago, USA) version 23.0 will be used for the analysis.

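### Withdrawal for completing under 80% of sessions, with no stated continued follow-up, conflicts with the intention-to-treat analysis

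*Protocol article*

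**What the plan says.** Under Withdrawal criteria the protocol article gives three items. The first is "Participant’s decision to drop out from study at any time for any reason". The second is non-adherence to the treatment protocol, specified as "patients who complete < 80% of the treatment session". The third is the occurrence of unexpected serious side effects. The section does not say whether assessments continue after a patient meets a criterion.

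Allocation comes before any treatment: patients are assigned to the active or "sham acupuncture group (placebo-control group) after the baseline assessment". The Active acupuncture group section fixes the course: "A total of 16 sessions of acupuncture treatment will be administered to each participant". The diary, questionnaires and urinary NGF are due at baseline, Week 8 and Week 20 (Outcomes, Table 2).

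Under Statistical analysis: "All analyses will be conducted according to the intention-to-treat principle". A second analysis is added: "Per-protocol analysis will be also performed". The model is named as follows: "The generalized linear mixed model will be used to compare primary and secondary outcomes between groups".

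**The concern.** Intention to treat needs two things: patients are analysed in the arm to which they were allocated, and adherence after allocation does not decide who is measured. A rule that withdraws patients for low attendance breaks the second condition if withdrawal ends assessment. The analysis called intention-to-treat would then rest mainly on patients who attended at least 80% of sessions and had no unexpected serious side effect. The per-protocol analysis would use much the same patients, so agreement between the two would say little about robustness.

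An analysis plan cannot repair this afterwards, because it cannot recover diaries that were never collected. The mixed model helps little. A patient with only a baseline value adds almost nothing to the between-group comparison, and validity then rests on a missing-at-random assumption. That assumption is doubtful if patients stop attending because they see no benefit or tolerate the sessions poorly.

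Attendance could differ by arm. The Sham acupuncture group section says that sham patients feel a prick without the de-qi sensation, and the Blinding section says that the acupuncturists know the allocation.

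**Working it through.** **1. When the adherence rule applies.** Planned sessions: 16 (Active acupuncture group). 0.80 × 16 = 12.8. Since 13/16 = 81.25% and 12/16 = 75%, the rule is met at 12 or fewer sessions, that is, at the fourth missed session. This falls during treatment or at its end, so a patient who then leaves the study may have only a baseline value of the primary outcome.

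**2. The plan's own figures.** The Sample size estimation section states 41 per group. Reading its 40% and 40% + 30% = 70% as proportions of patients, two-sided 0.05, 80% power, pooled variance:

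n = [1.96 × √(2 × 0.55 × 0.45) + 0.8416 × √(0.4 × 0.6 + 0.7 × 0.3)]² / 0.30² = (1.379 + 0.565)² / 0.09 ≈ 42, one more than stated.

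The 20% dropout allowance gives 41 × 1.2 = 49.2, hence 50 per arm. The plan therefore treats dropouts as supplying no outcome. A 20% loss leaves 0.8 × 50 = 40 per arm, one below 41. On the same reading, power is 0.78 with 40 per arm and 0.87 with all 50 observed. The present point does not depend on this calculation.

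**3. The sections side by side.** Withdrawal criteria: attendance after randomisation is a ground for withdrawal, listed beside dropping out of the study. Statistical analysis: all analyses by intention to treat, with a separate per-protocol analysis. No section shown says that patients below 80% are still assessed at Week 8 and Week 20.

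**4. Possible effect on the estimate (assumed figures).** Suppose that completers show reductions of 70% (active) and 40% (sham), a difference of 30 points.

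- 20% of active and 10% of sham withdrawn, each with a 20% reduction: (0.8 × 70 + 0.2 × 20) − (0.9 × 40 + 0.1 × 20) = 60 − 38 = 22 points. With no reduction in the withdrawn: 56 − 36 = 20 points.
- Rates swapped (10% active, 20% sham): (0.9 × 70 + 0.1 × 20) − (0.8 × 40 + 0.2 × 20) = 65 − 36 = 29 points. With no reduction in the withdrawn: 63 − 32 = 31 points.

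Against the completers' 30 points, the first case overstates the effect by 36% to 50% (30/22 and 30/20). The second hardly changes it.

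**5. Possible effect on type I error (simulation, assumed inputs).** No true effect, normal outcome with SD 1, 50 randomised per arm, withdrawal more likely with a poor outcome, two-sided test of the remaining patients, 20,000 replicates. Positive bias favours acupuncture.

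| Withdrawn, active / sham | Correlation of withdrawal with outcome | Bias (SD) | Type I error |
|---|---|---|---|
| 20% / 20% | 0 to 0.7 | 0.00 | about 5% |
| 10% / 30% | 0 | 0.00 | about 5% |
| 10% / 30% | 0.3 to 0.7 | −0.09 to −0.21 | 7% to 18% |
| 30% / 10% | 0.3 to 0.7 | +0.09 to +0.21 | 7% to 18% |
| 5% / 35% | 0.3 to 0.7 | −0.14 to −0.32 | 9% to 35% |

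Bias arises only when withdrawal is related to outcome and also differs by arm. Its sign follows the arm that loses more patients.

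**The case against.** The strongest reply is that the loss of later diaries is inferred. Only the first withdrawal item mentions the study; the adherence and side-effect items do not say that data collection ends. The Outcomes section says that all outcomes are collected at all three times, with no exception. Naming both an intention-to-treat and a per-protocol analysis suggests two different sets, and 80% attendance is a natural per-protocol boundary. The article also condenses a fuller protocol, and its flow chart and schedule figure are not visible.

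This stands as a limit on certainty. It does not remove the conflict. The rule is stated, it sits in one list with leaving the study, and nothing shown exempts these patients from its ordinary meaning.

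Three stronger readings are tempting and should not be drawn:

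- A reader might infer that the trial will overstate acupuncture by a third to a half. That comes from assumed withdrawal rates, and swapping them between arms removes it. Patients are blinded and the sham device hides whether the needle penetrates, so differing attendance is possible but not shown.
- A reader might infer that safety follow-up of harmed patients is lost. The Adverse events section records onset, intensity, outcome and resolution of every event and does not stop at withdrawal.
- A reader might infer that the intention-to-treat analysis is certainly defeated. It is not if these patients are in fact still assessed and analysed as randomised. The document does not say that they are.

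**Conclusion.** The concern holds as a conflict between the Withdrawal criteria and the Statistical analysis section. On its natural reading, the rule lets attendance, or an unexpected serious side effect, decide after randomisation who is measured at Week 8 and Week 20. The two analysis sets would then largely coincide. This rests on the inference that withdrawal ends outcome assessment.

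The size and direction of any bias cannot be computed from the document. On the assumed inputs above, it runs from none to about 0.3 SD in either direction. The matter is more than missing detail, because the primary comparison depends on data that a later analysis plan could not restore.

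**What to change.** Reconcile the two sections by separating stopping of study sessions from withdrawal from follow-up:

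- State that patients who meet the adherence or side-effect criterion are still asked for the diary, questionnaires and urine NGF at Weeks 8 and 20, unless they withdraw consent for this, and are analysed as randomised.
- Use the 80% threshold only to define the per-protocol set.
- For patients already withdrawn without outcomes, report numbers and reasons by arm and add a sensitivity analysis for the missing data.

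The third step matters because of timing. The article appeared on 13 July 2018 and the anticipated end is 31 August 2018. If that date includes Week 20, the last patient started by about 13 April (20 weeks earlier) and reached Week 8 by about 8 June. Missed Week 8 diaries could then no longer be collected.

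The cost is a short clarification, some effort to obtain outcomes from patients who stopped attending, and one added analysis. No treatment rule changes.
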